#### Three-dimensional postural parameters

A GPS (Chinesport, Italy) will be used to assess the 3-DPPs. The device has a unit for podoscopic analysis, a unit for postural analysis and a stability measuring platform, and it comes with an image acquisition system and custom software. The camera of the image acquisition system will be positioned 107 cm from the ground and 190 cm from the subject. The protocol published by Youssef’s group [49] will be used to analyze each subject’s posture in the coronal and sagittal planes.

##### Assessment environment

The 3-DPPs’ assessments will take place in a private, warm, well-lit room with flat-white walls.

##### Preparation of the GPS

The GPS device must be adjusted to a standard position before the assessment.

##### Preparation of the subjects

The subjects will be instructed to remove their clothes and wear only their underwear. They will then stand naturally with their feet shoulder-width apart while 11 round, reflective, red stickers 5 mm in diameter are attached to their body.

##### Marker placement

The posterior view markers will include eight round, reflective, red stickers and will be placed on the following anatomical landmarks: right and left acromia, two spinous processes (C7, S1), the right and left inferior angles of the scapula, and the posterior superior iliac spine.The right lateral view markers will include three round, reflective, red stickers and will be placed on the following anatomical landmarks: right tragus, right canthus, and right anterior superior iliac spine.

##### Photo acquisition

The subjects will be asked to place their feet on standard footprints, to stand naturally and to take 3 deep breaths to relax the body. The subjects’ back and right side will then be photographed.

##### Posture parameter analysis

The images will be processed by the GPS system’s software to measure the angles and distances between the markers. Estimates of the sagittal head angle, craniovertebral angle, protracted shoulder angle, shoulder alignment, scapula asymmetry, right and left waist angle, frontal pelvic tilt, sagittal pelvic tilt right, C7 alignment, and S1 alignment will be generated. Fortin’s method [50] will be used to calculate the angles and distances*.* Some details are shown in Additional file 3.

The same assessor with 4 years of experience using the GPS equipment will complete all of the subject assessments. The reliability and validity of this device has been verified in previous studies [51, 52].

#### SRS-22

The SRS-22 questionnaire is widely used for assessing the quality of life of individuals with scoliosis. It has five dimensions: functional activity, pain, self-image, psychological status, and satisfaction with treatment. The first four dimensions each contain five items, and the treatment satisfaction dimension contains two items. Each item has a maximum score of 5 and a minimum score of 1 point. The score for a dimension is the average of the scores for the items included in the dimension, so the scores range from 1 to 5. We will calculate the average score for each dimension and the total score for all dimensions. We will use the simplified Chinese version [53] of the questionnaire with question 15 modified to be filled in by the parents [54].

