### Eligibility

The inclusion criteria will be as follows [33]:
Age of 10–18 years.A diagnosis of idiopathic scoliosis.Cobb angle of 10–25°.Risser sign of 0–2.Agree not to receive any other treatments for scoliosis such as brace and insoles during the study period.

The exclusion criteria will be as follows:
Contraindications for exercise, such as cardiovascular or respiratory insufficiency.Contraindications for SMT, including inflammation, infection, advanced degeneration, congenital malformations, trauma, and cerebrovascular anomalies [34].A history of spinal surgery.A history of scoliosis treatment involving surgery, a brace, exercise, etc.

In addition to the simple unwillingness to continue, factors that can prevent a subject from continuing to participate, such as a new diagnosis of a severe disease, will be considered valid grounds for withdrawal.

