### Assessment

Age, sex, height, weight, Risser sign, menarche status (for the girls), and type of scoliosis will be recorded at the start of the experiment. The United States Risser staging will be used to quantify skeletal maturity on a scale of 0 to 5 [43]. Stage 0 represents no ossification of the iliac apophysis, whereas stage 5 represents complete ossification and fusion. The scoliosis types will include thoracic, lumbar, thoracolumbar, and S-shaped scoliosis, corresponding to the anatomical site of the spinal deformity [1].

The primary outcome will be the feasibility of performing a full-scale study using these protocols. The time to complete enrollment, recruitment rate, subject retention, and adherence to the treatment allocation will all be important observations. The efficacy of treatment will be the secondary outcome. Spine curvature, rotation of the trunk, and postural symmetry will be assessed by the Cobb angle from X-ray images; the ATR, as measured with a Scoliometer; and 3-DPPs, as measured using a global postural system (GPS), respectively. The SEP will be assessed for evaluating sensorimotor integration, and the SRS-22 will be administered for the quality of life. The Cobb angle will be measured at baseline and at the end of 8 weeks of training. The SEP will be measured at baseline and at the end of 2 weeks of training. The ATR, 3-DPPs, and SRS-22 scores will be measured at baseline and then after 2 weeks, 4 weeks, and 8 weeks of treatment. The mean changes of Cobb angle from baseline to the end will be compared. And the mean difference of other indicators between each two visits will be used for comparative analysis.

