### Data collection, data management, and statistical analysis

The primary outcome measures will be tabulated and interpreted with respect to the goals established a priori.

To estimate the sample size required for a future full-scale RCT, between-group effect sizes and their 95% confidence intervals will be calculated by applying Hedges’ correction. A minimum power of 80% will be used to detect changes in the Cobb angles, ATRs, 3-DPPs and SRS-22 scores (*α* = 0.05). The sample size will be increased to allow for an estimated 20% dropout rate. Statistical methods for the secondary outcome measures will be evaluated via comparisons of changes between groups.

The data will be double entered into EpiData 3.1 software (The EpiData Association, Odense, Denmark) and then transferred to version 22.0 of the SPSS software suite (IBM, Armonk, NY, USA) for the analyses. The threshold for significance will be taken as *α* ≤ 0.05. A statistician who will be blinded to the allocation results will analyze all the data. The continuous variables will be presented as means ± SDs, and the categorical variables will be presented as ratios. The baseline readings will be compared using independent samples *t* tests or chi-squared tests. For the Cobb angles and SRS-22 scores, independent samples *t* tests will be used to compare the two groups, and paired *t* tests will be used for within-group comparisons. For the M, U, MU, and M+U SEP peak amplitudes and latencies, nonparametric Wilcoxon signed-ranks tests will be used to compare these values between and within the groups. For the 3-DPPs and ATR, repeated measured analysis of variance will be used for the between-groups and within-groups comparison. Furthermore, we will perform subgroup analysis by age group (age < 13 years and age ≥ 13 years) [2, 33]. To deal with the missing data, a sensitivity analysis and weighted estimating equations will be used as the primary approach [61].

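### SRS-22 change from baseline includes satisfaction with treatment, which eligible subjects have little or nothing to rate at baseline; the change score should leave that dimension out

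*Protocol article*

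**What the plan says.** All of the following is in the protocol article.

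- SRS-22 section: "It has five dimensions: functional activity, pain, self-image, psychological status, and satisfaction with treatment". The first four dimensions have five items each, and "the treatment satisfaction dimension contains two items". On item range: "Each item has a maximum score of 5 and a minimum score of 1 point". On scoring: "We will calculate the average score for each dimension and the total score for all dimensions". Whether the total is a sum, an item mean or a mean of dimension scores is not stated.
- Assessment section: "The ATR, 3-DPPs, and SRS-22 scores will be measured at baseline and then after 2 weeks, 4 weeks, and 8 weeks of treatment". For outcomes other than the Cobb angle: "And the mean difference of other indicators between each two visits will be used for comparative analysis".
- Data collection, data management, and statistical analysis: "Statistical methods for the secondary outcome measures will be evaluated via comparisons of changes between groups". For the SRS-22 this means independent-samples t tests between groups and paired t tests within groups.
- Eligibility section, among the exclusions: "A history of scoliosis treatment involving surgery, a brace, exercise, etc".
- Primary outcomes, under the items on the primary outcome measure and the sample size: the future trial's primary endpoint is to be the secondary outcome with the largest between-group effect size, and that trial is to be sized from the pilot's effect sizes. The statistical section names the SRS-22 among the outcomes used for sizing.

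No sentence restricts the satisfaction dimension to visits after treatment has begun or takes it out of the total.

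**The concern.** The sentence on SRS-22 scoring only defines scores. The difficulty appears when it is read with the visit schedule, the change analysis and the exclusions. Followed as written, the plan subtracts a baseline rating of treatment satisfaction in adolescents selected for not having had scoliosis treatment. A paired test of that dimension from baseline then has no defined starting point, and the total inherits part of the problem.

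Two things are at stake. First, a paired test on the total could show a quality-of-life gain within a group when only the satisfaction items have moved. Second, the SRS-22 effect size is a candidate for choosing and sizing the next trial's endpoint, so its content matters more here than for an ordinary secondary outcome.

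**Working it through.** The plan states no figure on this point, so there is none to reproduce. The check has three steps.

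**1. Weight of satisfaction in the total.** Inputs from the SRS-22 section: four dimensions of 5 items and one of 2, so 4 × 5 + 2 = 22 items, each scored 1 to 5.

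- As an item mean, the weight is 2/22 = 9.1%. A 1-point shift in both items moves the total by 2 × 1/22 = 0.09.
- As a mean of the five dimension scores, the weight is 1/5 = 20%. The same shift moves the total by 1/5 = 0.20.
- As a sum of items, it moves the total by 2 points.
- The largest possible shift, from 1 to 5 on both items, gives 2 × 4/22 = 0.36, 4/5 = 0.80 or 8 points. This is a bound, not an expected size.

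**2. Effect on the planned tests, by illustration.** The article gives no SDs for the SRS-22, so these are assumptions. There are 17 evaluable subjects per arm (the article's figure for the Cobb angle). Each of the four ordinary dimensions has a visit-to-visit error SD of 0.35. Satisfaction is pure noise at baseline (SD 0.8) and has SD 0.6 after treatment. All are independent and treated as continuous.

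SD of the change scores:

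- One ordinary dimension: variance 2 × 0.35² = 0.245. Satisfaction: variance 0.8² + 0.6² = 1.00.
- Four-dimension mean, equal to the 20-item mean because each has 5 items: √(0.245/4) = 0.247.
- 22-item mean: √(4 × (5/22)² × 0.245 + (2/22)² × 1.00) = 0.243.
- Five-dimension mean: √(4 × 0.2² × 0.245 + 0.2² × 1.00) = 0.281.

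*Within a group*, with no change in the other four dimensions and satisfaction up by 1 point in both arms, the noncentrality of the paired t test is shift × √17 / SD:

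- 22-item mean: 0.0909 × 4.123/0.243 = 1.54. In 20,000 simulated trials the test was significant in about 31%.
- Five-dimension mean: 0.20 × 4.123/0.281 = 2.93. Significant in about 79%.
- Four-dimension mean: shift 0. Significant in about 5%.

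*Between groups*, in the same setting, the difference in mean change was 0.00 and the test was significant in about 5% of trials for either form of total. Both arms share the uninformative baseline. With a 0.3-point effect on every dimension, power was about 0.93 for the four-dimension mean, 0.94 for the 22-item mean and 0.85 for the five-dimension mean. The noise therefore costs visible power only if the total weights dimensions equally.

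**3. What the between-group effect size contains.** Suppose that, after treatment, the arms differ by 1 point in satisfaction and in nothing else. Under the same assumed SDs, before Hedges' correction, the standardised difference in change is 0.0909/0.243 = 0.37 for the 22-item mean, 0.20/0.281 = 0.71 for the five-dimension mean, and 0 for the 20-item subtotal. The 1-point difference is hypothetical; the calculation shows only that satisfaction alone can produce an apparent SRS-22 effect.

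**The case against.** The strongest reply is that the planned contrast for secondary outcomes is between groups, and randomisation protects it. This stands. A reader might infer that the change in the total is invalid altogether. The documents do not support that: 20 of the 22 items have an ordinary baseline, an arbitrary satisfaction baseline is balanced in expectation, and differences between two visits after baseline (2 to 4, 4 to 8 and 2 to 8 weeks) are untouched.

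A second reply is that the article does not show the wording of the two items, their response options or the rule for blank items, and the cited questionnaire version is not at hand. The exclusion is broad, but a subject seen in an outpatient department could have had observation or advice and might rate that. This also stands in part: the missing referent is a strong inference from the eligibility rule, not a stated fact. For the same reason, a reader might infer that all 40 subjects would lack a baseline total; that is a possibility the documents neither state nor exclude.

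A third reply is that an attention effect comes from lack of blinding, not from the baseline. That is right. The study group receives 5 + 10 + 15 = 30 further minutes per session in the first 2 weeks, and subjects know their allocation. This would influence self-report even with a perfect baseline, and it can reach pain, self-image and psychological items that the subtotal keeps. What remains is narrower: satisfaction is plausibly the dimension most exposed, and including it in the total reports it as a change in quality of life.

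**Conclusion.** The concern holds in a limited form. Change from baseline in the satisfaction dimension is not interpretable. The within-group change in the total is contaminated, by 0.09 (item mean) or 0.20 (mean of dimensions) for each point of satisfaction shift. The between-group change is not biased by the baseline, only made noisier, but it brings unblinded post-treatment satisfaction into an effect size that may influence which endpoint the future trial uses and how large that trial is.

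The weights follow from the item counts alone. The 31% and 79% figures, the power values and the standardised differences rest on assumed SDs and shifts and are illustrations only. It would be too strong to read 0.36 as the likely distortion: that requires everyone to move from the lowest to the highest score on both items, and as a between-group effect it also requires no movement in the other arm. The trial's primary outcome, feasibility, is not affected.

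**What to change.** Make two edits to the protocol.

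1. In the SRS-22 section, define a 20-item subtotal of function, pain, self-image and psychological status, state that it is the mean of those items, and name it as the SRS-22 change outcome.
2. In the statistical analysis section, use that subtotal for the tests of change and for the effect size that feeds endpoint choice and sample size. Compare satisfaction between groups as post-treatment values at 2, 4 and 8 weeks, without subtracting baseline. All three visits follow the start of treatment, so there is no reason to keep only the 8-week value. Label the comparison as an unblinded self-report.

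The scheduled questionnaires already supply the data. In the illustration above, the subtotal gives up about 0.01 in power against the 22-item mean and gains about 0.08 against the five-dimension mean. The downside is that the full total is no longer the change score, which slightly limits comparison with studies that report it; it could still be tabulated descriptively at each visit.

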### Adverse events

Adverse events during SMT can be classified as mild (transient effects lasting fewer than 24 h), moderate (requiring medical treatment), or severe (requiring hospitalization) [55]. Severe adverse events are rarely reported with SMT [56, 57], but mild and moderate adverse events are common, though self-limiting. Most occur within 24 h and resolve without treatment within 72 h [56]. Almost all of the severe adverse events attributable to SMT are related to cervical manipulation and underlying pre-existing pathologies [57, 58].

In this trial only SMT of the thoracic, lumbar, and sacral segments will be administered. The cervical segments will not be involved. And subjects with pre-existing pathologies detected in systematic physical examinations and spinal X-ray examinations will be excluded. Considering that all the subjects in this study will be adolescents, the HVLA process will be performed carefully and the force of the manipulation will be adjusted according to the age and condition of the subject. Adverse events should therefore be few and relatively minor. In the first 2 weeks, the therapist will inquire about adverse events daily via telephone. In the next 6 weeks, weekly follow-up via telephone will be conducted by the same therapist. Subjects will also be required to contact the therapist if they experience pain, transient headache, or any other discomfort that may be relevant to treatment. If the discomfort does not disappear within 24 h after treatment, the SMT will be discontinued. Any adverse events observed will be recorded and reported to the supervising ethics committee, regardless of their severity. Additionally, both predictable potential adverse events (e.g., crying, pain, or transient headache, etc.) and unpredictable adverse events hindering the health of subjects happened in this trial will be reported truthfully in future publications.

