#### Spinal manipulative therapy

In the first 2 weeks, the study group will additionally receive SMT before PSSE 5 times a week. SMT will involve 5 min of evaluation, 10 min of soft tissue relaxation techniques, and 15 min of HVLA manipulation.

Before SMT is performed, it is necessary to evaluate and find the dysfunctional spine segments. Pain and tenderness during palpation or the examination of local tissue are the primary indicators used for identifying the dysfunctional segments [39]. Restricted joint mobility during the spinal examination is also an important indicator [39]. In this study, if the physiotherapist finds any pain, tenderness, or restricted joint mobility when assessing the region from C7 to S1 and the sacroiliac joints, the segments involved will be defined as dysfunctional and recorded as target segments for treatment. For thoracic and lumbar segments, the alignment of the spinous processes is assessed with unilateral or bilateral fingertip contacts. Any potential tenderness or pain around the spinous processes and soft tissues will be recorded. In addition, coupled lateral flexion and rotation movements will be induced on both sides in the extended and flexed positions. For example, the examiner will stand on the subject’s left side, place his right thumb on the right thoracic spinous process, and guide the subject’s upper body with his left hand from a neutral and upright sitting position into rotation and lateral flexion position until the movement reaches the palpating thumb. During the examination, if the subject complains of pain or the examiner observes asymmetric motion between the left and right sides, that means the segments are dysfunctional. For the sacroiliac segments, the subjects will stand barefoot on a firm surface, and the therapist will first palpate the posterior superior iliac spine on both sides and assess the asymmetry as well as the presence of any pain or tenderness during palpation. The positions of the bilateral sacroiliac joint surface projections will be assessed at the same time. The evaluation procedure will be based on that described in chapters 9 to 11 of the palpation techniques book: surface anatomy for physical therapists [40].

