After the examination of all segments is completed, the therapist will perform 10 min of soft tissue relaxation on the dysfunctional segments by using rolling manipulation, a form of traditional Chinese massage. The subjects will be instructed by the therapist to lie in the prone position and to relax their mind and body. The therapist will contact the treatment site with the dorsal side of his fifth metacarpophalangeal joints and then sink the shoulders and loosen the wrists, with the elbow joint serving as the support. The forearm will actively swing, driving flexion and extension of the wrist joint and rotation of the forearm. The metacarpophalangeal joints will be rolled back and forth on the treatment site at a frequency of 120–160 times/min [41].

After soft tissue relaxation, the therapist will perform HVLA manipulation on the dysfunctional segments to address the subject’s pain, muscle tension, and limited segmental activity. Figure 4 outlines the main HVLA manipulation procedures in our research. For example, Fig. 4c outlines the HVLA technique for adjusting the extension of middle thoracic section. To induce extension with the patient in the supine patient position, the thenar contacts are typically established over the transverse processes of the inferior vertebral segments. The joint to be adjusted is bent into extension over the top of the posterior contact, and the therapist exerts a force posteriorly, using body weight to induce distraction in the joints above the contact. All HVLA manipulation methods will be based on that described in chapter 5 of the chiropractic technique book [42]. The treatment will be stopped immediately if discomfort occurs. One physiotherapist with 10 years of HVLA manipulation experience will perform all the examinations and manipulations.

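### The safety section rules out cervical manipulation, but the treatment procedure permits a thrust at C7 or the C7/T1 joint

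*Protocol article*

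**What the plan says.** The Adverse events section gives the scope of treatment without qualification: "In this trial only SMT of the thoracic, lumbar, and sacral segments will be administered", followed by "The cervical segments will not be involved". It explains why this matters: "Almost all of the severe adverse events attributable to SMT are related to cervical manipulation and underlying pre-existing pathologies". After the cervical exclusion it adds exclusion of pre-existing pathology, careful delivery, and force adjusted to the subject's age and condition. It then concludes: "Adverse events should therefore be few and relatively minor".

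The Spinal manipulative therapy section gives the working rule. If the physiotherapist "finds any pain, tenderness, or restricted joint mobility when assessing the region from C7 to S1 and the sacroiliac joints", then "the segments involved will be defined as dysfunctional and recorded as target segments for treatment". After soft tissue work, "the therapist will perform HVLA manipulation on the dysfunctional segments". The text presents Fig. 4 as the trial's main HVLA procedures, and the Fig. 4a legend gives the range of one prone technique as C7 to T4.

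**The concern.** C7 is a cervical vertebra. The procedure names it as the top of the region in which findings become treatment targets, and a listed thrust technique has a range that starts there. The safety section says no cervical level is treated. A therapist who follows the procedure can therefore deliver a thrust that the safety section says will not happen.

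What is at stake is a safety assurance about subjects aged 10 to 18, who receive SMT five times a week for two weeks. The article itself links severe SMT events to cervical manipulation and uses the cervical exclusion as one ground for expecting little harm. Someone relying on that section would believe that no cervical level can be thrust, and the written procedure does not secure this.

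**Working it through.** The article states no figure on this point, so the check sets the texts side by side and then counts the levels involved.

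**Following the procedure as written**

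1. The assessed region runs from C7 to S1 plus the sacroiliac joints (Spinal manipulative therapy). C7 is inside it.
2. Pain, tenderness or restricted mobility in that region makes the segment dysfunctional and a treatment target (same section). Tenderness at C7 or stiffness at C7/T1 meets this rule.
3. Dysfunctional segments receive HVLA manipulation (same section).
4. A technique whose stated range begins at C7 is available (Fig. 4a legend).
5. No cervical segment is to receive SMT (Adverse events). Steps 1 to 4 permit what this rule forbids.

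**Looking for a limiting statement**

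- The detailed examination is described only for other levels: "For thoracic and lumbar segments, the alignment of the spinous processes is assessed", and then the sacroiliac joints. This suggests that cervical treatment may not be intended, but it does not narrow the target rule, which names C7.
- Marker placement uses C7 and S1 as surface points for posture photographs. That is outcome measurement, not SMT.
- No section says that C7 is only a landmark for SMT or that the thrust stops at T1.
- The Fig. 4 labels are not fully consistent: Fig. 4c is described as middle thoracic in the text and upper thoracic in the legend. Fig. 4a is therefore supporting evidence. The main conflict is between the target rule and the Adverse events statement.

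**Extent of the conflict** (counting 12 thoracic and 5 lumbar vertebrae, and S1 as one level)

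| Item | As printed | If started at T1 |
|---|---|---|
| Target region | C7 to S1: 1 + 12 + 5 + 1 = 19 levels, 1 cervical | T1 to S1: 12 + 5 + 1 = 18 levels, 0 cervical |
| Fig. 4a | C7, T1, T2, T3, T4 = 5 levels, 1 cervical | T1 to T4 = 4 levels, 0 cervical |
| Intervertebral joints | C7/T1 to L5/S1 = 18 | T1/T2 to L5/S1: 11 + 1 + 4 + 1 = 17 |

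The last cell holds only if C7/T1 is excluded in words. A range written as T1 to T4 does not say whether the joint above T1 may be thrust, so the count could still be read as 17 or 18.

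Starting Fig. 4a at T1 leaves no gap among the prone techniques. T1 to T4 (4 levels) plus T3 to T8 (6 levels), less the shared T3 and T4 (2 levels), gives 8 levels, T1 to T8.

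These counts describe the extent of the wording conflict. They do not measure risk.

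**The case against.** The best defence is that the two sections answer different questions. The procedure gives the region assessed, the safety section gives what is administered, and the specific treatment limit governs. On this reading C7 only marks the top of the region, which fits the absence of any cervical examination. This is possible, but the article does not say it, and the procedure does more than define an assessment range: it turns findings in that range into treatment targets.

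A second defence is that the Fig. 4a range means motion segments starting at C7/T1, with contact on T1. The one worked example, Fig. 4c, does place the contact on the lower vertebra of the joint. The article does not extend this to Fig. 4a, whose image is not available here, and in any case the C7/T1 joint would still be thrust. What stands is that a thrust on C7 itself is not established as planned; the text permits it, and leaves the status of the C7/T1 joint unsettled.

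The objection that no harm is shown also stands. The article does not say that the risk it attaches to cervical manipulation extends to the cervicothoracic junction. Other protections are unaffected: SMT contraindications, including cerebrovascular anomalies, are excluded; one therapist with 10 years of HVLA experience delivers all treatment; treatment stops at once on discomfort; and adverse events are asked about daily in the first two weeks. These points keep the finding minor but do not reconcile the two statements.

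**Conclusion.** The concern holds. The unqualified cervical exclusion and the C7-to-S1 target rule cannot both be followed when a finding falls at C7 or C7/T1. The size is minor: one boundary level, one joint, and no effect on sample size, randomization, endpoints or analysis. The conclusion rests on counting C7 as cervical and on reading the target rule as printed. It does not assert that cervical treatment is intended or that any subject has been thrust at C7; actual exposure is unknown. The consequence is that one of the article's stated reasons for expecting few and minor adverse events is not secured by its own procedure.

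**What to change.** The investigators know which contact point Fig. 4a shows and should choose one of two corrections.

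- **If the junction is not to be treated:** in Spinal manipulative therapy, change the assessed region to T1 to S1 and the sacroiliac joints; change the Fig. 4a legend to T1-T4; and add to Adverse events: *No thrust will be applied to C7 or to the C7/T1 joint.* The added sentence is needed because the range alone leaves C7/T1 open. Figs. 4b to 4f stay as they are, and no thoracic, lumbar or sacroiliac level loses its listed technique.
- **If the junction may be treated:** amend Adverse events to say that C7/T1 may be manipulated, and remove the unqualified cervical exclusion from the safety reasoning.

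In either case, look through the target segments already recorded for C7. Trial status gives November 2019 as the start of recruitment, so subjects may already have been treated under the present wording.

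The cost is two phrase edits and one added sentence, or one amended statement, plus a review of records the procedure already requires. No new data are collected and the analysis does not change.
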